## Exclusion Criteria

# 1. Currently receiving oral ergocalciferol at any dose

# 2. Received IM ergocalciferol therapy within last 3 months

# 3. Receiving renal replacement therapy of any type or having recently received any form of dialysis (within 3 months)

# 4. Pacemaker or any other implanted cardiac device

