## Prior and Concomitant Therapies

Prior therapies:

There will be a washout period of 2 weeks for all vitamin D therapies currently being taken by participants. The most commonly prescribed oral vitamin D analogues all have a half life of less than 14 days (Alfacalcidol— 3 hours, Calcitriol—3 to 6 hours, Ergocalciferol—19 to 48 hours) (34). Participants will be screened for use of all over the counter medicines which may contain vitamin D. It is very unlikely patients will suffer any side effects from stopping these medications for this period. Patients will be reassured about the safety of drug withdrawal and the safety and validity of undertaking a randomized, placebo controlled trial. Given that routine supplementation with vitamin D in early CKD is not routine, we anticipate that very few individuals will actually need to stop vitamin D analogues.

The patient’s general practitioner will be contacted to ensure no medicines that may contain vitamin D are being taken by participants without their prior knowledge and that no depot vitamin D preparations have been dispensed in the last 6 months.

Concomitant therapies:

Blood pressure medication should be unchanged for study period but additional therapies can be added at the discretion of the investigators if blood pressure requires clinical intervention on safety grounds. General practitioners will be asked to maintain BP medications at a stable dose. Any changes in medication by the study team will be communicated to GP’s in writing and included in the CRF. Patients will be asked to take any concomitant therapies which can affect microvascular function after clinic visits at which these assessments are made (visits 2,3,4,6,9)

Drugs which are likely to have these particular effects include aspirin and vasodilating anti-hypertensives such as calcium channel blockers. There is no evidence to suggest that iontophoresis of acetylcholine (Ach) and sodium nitroprusside (SNip) is directly affected by the presence of any antihypertensive drugs. However, there is a theoretical chance that there may be some affect on vasodilatiation particularly by drugs with a known vasodilatory effect eg calcium channel blockers. Hence, patients will be asked to take all their daily medications after all microcirculatory assessments have been made.

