# Study Procedures and Schedule of Assessments

Patients will be examined and assessed by an investigator at the renal outpatient department of the Royal London Hospital. Cardiac MRI will take place at the London Chest Hospital (aprox 20 min walk from RLH)

All assessments will be similar between the two groups. At each study point, participants will undergo the relevant assessment and will also receive one dose of the study drug to ensure compliance.

The table below details each study time point and exactly what will occur. Each Action is explained in more detail below.

| **Visit** | **Drug** | **Action** | **Action** | **Action** | **Action** | **Action** | **Action** | **Action** | **Action** | **Action** |
| --- | --- | --- | --- | --- | --- | --- | --- | --- | --- | --- |
| 0 weeks | Washout |  |  |  |  |  |  |  | Bloods | Examination |
| 2 weeks | n |  | Microcirc |  |  |  |  |  |  | Examination |
| 1 month (4 weeks) | y | ECG | Microcirc | SF 36 | Urine | MRI/echo | 24hr BP | USS neck | Bloods | Examination |
| 2 month | y |  | Microcirc |  | Urine |  |  |  | Bloods | Examination |
| 3 months | y |  |  |  |  |  |  |  | Bloods | Examination |
| 4 months | y |  | Microcirc |  | Urine |  |  |  | Bloods | Examination |
| 5 months | y |  |  |  |  |  |  |  | Bloods | Examination |
| 6 months | y |  |  |  |  |  |  |  | Bloods | Examination |
| 7 months | n | ECG | Microcirc | SF 36 | Urine | MRI/echo | 24hr BP | USS neck | Bloods | Examination |

**Time** – 0 weeks refers to recruitment, consent and enrolment. Randomisation will occur at month 1 (4 weeks after recruitment). The study will end at month 7 after recruitment. Patients will receive the study drug for 6 months in total.

**Drug** – at month 1 (week 4) patients will be randomized to and receive at that visit either placebo or ergocalciferol. Patients will receive all 9 capsules of study medication at this time. They will be required to take 1 dose weekly at home in the first month. Further study medication will be taken at subsequent clinic visits and patients will be observed swallowing their medication either by pharmacy staff or an investigator.

**ECG** – a 12 lead cardiac ECG will be undertaken. This is a painless, non-invasive procedure.

Duration 5 minutes.

**Microcirc** – This process involves four assessments of the microcirculation and will take place at a clinic visit in the same room.

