# Ethical Considerations

General considerations:

The study will be conducted in accordance with the principles of the Declaration of Helsinki (1997) (Recommendations guiding Medical Doctors in Biomedical Research Involving Human Subjects).

Every effort will be made to minimize discomfort and disruption to the trial participants.

All relevant study documentation will be submitted to a National Research Ethics Service (NRES) and no trial activity will begin until approval from this body has been received. A copy of ethical approval will be forwarded to the sponsor. If ethical approval is suspended or terminated, the sponsor will be informed immediately. Trial progress will be reported to the ethics committee once a year. All SAE’s will be reported to the ethics committee as soon as possible and at least within 72 hours.

Study specific ethical considerations:

1. The endpoints of this trial (both in vivo and in vitro) have never been addressed in the setting of a randomized clinical trial. New and relevant information which will change practice to enhance patient care and could influence CKD guidelines can be generated by undertaking this study.

2. The study drug, ergocalciferol, is in routine use for vitamin D deficiency in a number of clinical settings. It has a low side effect profile and is considered to be safe and efficacious.

3. Placebo controlled trials have been in routine use in medical research for years. If a benefit is shown in the ergocalciferol arm, patients who have received placebo can be eligible for ergocalciferol treatment when the trial ends.

4. Secondary hyperparathyroidism (SHPT) is a recognized consequence of CKD and is treated by vitamin D therapy. It is possible that patients with modestly elevated PTH levels will receive placebo tablets. This means that their SHPT will go untreated for 6 months. However, an analysis of PTH levels in an existing group of patients at the Royal London Hospital with CKD and vitamin D deficiency has shown a low median PTH value (median 11.7, standard deviation 19.44 pmol/L). This level of PTH is unlikely to have any serious clinical consequences if not treated over the trial duration and we do not believe patients are at risk by potentially not receiving ergocalciferol. Patients will be reassured about the safety of the drug and the safety and validity of undertaking a randomized, placebo controlled trial.

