# Study Procedures and Schedule of Assessments

The follow up period has been shortened to three months. This will reduce the risk of hypercalcaemia and allow the investigators to determine if three months vitamin D therapy is sufficient to replenish vitamin D stores and modulate microvascular function. The total study duration for the additional arm is 4 months.

The table below details each study time point and exactly what will occur.

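### Patients taking a vitamin D analogue for secondary hyperparathyroidism can enter and be taken off it, but neither safety statement addresses loss of that treatment for the length of the trial

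*Combined protocol and SAP*

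**What the plan says.** **Entry.** The vitamin D items in Exclusion Criteria are "Currently receiving oral ergocalciferol at any dose" (item 1) and recent intramuscular ergocalciferol (item 2). Neither names alfacalcidol, calcitriol or any other analogue. Appendix 1 leaves the exclusions unchanged for the additional arm.

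**Stopping.** Prior and Concomitant Therapies says: "There will be a washout period of 2 weeks for all vitamin D therapies currently being taken by participants". It gives half-lives for alfacalcidol, calcitriol and ergocalciferol, and continues: "It is very unlikely patients will suffer any side effects from stopping these medications for this period". It adds: "Patients will be reassured about the safety of drug withdrawal". On numbers, "we anticipate that very few individuals will actually need to stop vitamin D analogues".

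**Timing.** The schedule table puts the washout at 0 weeks. For the main study, "Randomisation will occur at month 1 (4 weeks after recruitment). The study will end at month 7 after recruitment". In Appendix 1, "The total study duration for the additional arm is 4 months".

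**Placebo and SHPT.** Ethical Considerations, item 4, says that SHPT is treated with vitamin D, that some patients with mildly raised PTH will receive placebo, and that their SHPT will then be untreated for 6 months. It considers this acceptable because an analysis of local patients with CKD and vitamin D deficiency "has shown a low median PTH value (median 11.7, standard deviation 19.44 pmol/L").

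**The concern.** The protocol itself treats vitamin D as therapy for SHPT. It foresees that some entrants will be on an analogue and takes them off it. Randomisation then gives half of them placebo. The assurance about stopping is worded for the washout, and the half-lives behind it show how fast the drug clears, not what PTH does afterwards. The assurance for the longer period concerns a different situation: patients who do not receive ergocalciferol.

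At stake is the justification for withdrawing an existing treatment from a small group of patients, and the reassurance the protocol says they will be given about it. The validity of the efficacy comparison is not in question.

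**Working it through.** **1. Time off an analogue on placebo.** Inputs: washout at week 0, randomisation at 4 weeks, 6 months of study drug, end at month 7 (Study Procedures and Schedule of Assessments); 4 months in total for the additional arm (Appendix 1). One calendar month is 365.25/12/7 = 4.348 weeks.

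- The plan's own figure: 1 month (taken as 4 weeks) + 6 months = 7 months. This reproduces.
- Main study: 4 + 6 × 4.348 = 30.1 weeks. Seven calendar months give 30.4 and seven 4-week months give 28.
- Additional arm: 4 + 3 × 4.348 = 17.0 weeks. Four calendar months give 17.4.
- Randomisation is at 4 weeks, so the 2-week statement has run out before the first capsule is taken.

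**2. Is staying off stated or inferred?** It is inferred. No section provides for a restart and none expressly forbids one. Four things support the inference:

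- The general practitioner is contacted to make sure that no products containing vitamin D are being taken.
- Inclusion criterion 7 has the patient agree to avoid, during the study, medicines that the principal investigator judges clinically significant.
- A new drug triggers a decision on withdrawal (Prior and Concomitant Therapies).
- The comparator is placebo.

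**3. What each safety statement covers.**

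| Statement | Period | Situation |
| --- | --- | --- |
| Prior and Concomitant Therapies | the 2-week washout | stopping vitamin D products |
| Ethical Considerations, item 4 | 6 months, the trial duration | mildly raised PTH, ergocalciferol not given |
| Neither | about 30 weeks (17 in the additional arm) | existing SHPT treatment withdrawn, then placebo |

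Item 4 does not say whether the local patients were on treatment. Its basis is also a median. A non-negative quantity symmetric about 11.7 would lie between 0 and 23.4, so its SD could not exceed 11.7. The stated SD is 19.44, so the distribution is skewed to the right and the median does not describe the higher values.

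**4. How many patients.** The protocol gives no number beyond very few. Take p as the share of entrants on an analogue; the values are assumptions. With 40 on placebo, the expected number is 40p and the chance of at least one is 1 − (1 − p)^40.

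| p | Expected on placebo | Chance of at least one |
| --- | --- | --- |
| 1% | 0.4 | 33% |
| 2% | 0.8 | 55% |
| 5% | 2.0 | 87% |

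**5. Cost of excluding them.** Otherwise eligible patients needed to enrol 80 are 80/(1 − p), rounded up: 80.8 → 81, 81.6 → 82, 84.2 → 85.

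**The case against.** The strongest reply is that the long period is disclosed. Ethical Considerations, item 4, says openly that SHPT will be untreated for 6 months and gives a safety view for that time. A reader might divide 30 weeks by 2 and conclude that the protocol's cover falls short 15-fold. The documents do not support that. Against the 6 months in item 4 (6 × 4.348 = 26.1 weeks), the extra time is 30.1 − 26.1 = 4.0 weeks. This part of the reply stands. What remains is a gap in the situation covered, withdrawal as opposed to non-provision, more than in length.

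Second, there is monitoring. Calcium and PTH are in the routine blood panel, out-of-range results go to an investigator (Laboratory Assays), and patients are reviewed at each visit (Medical Monitoring). Withdrawal of Subjects lets a patient stay in the study on a new medicine judged not to interfere. This too stands: a problem would probably be seen, and a restart is not ruled out. It does not supply the missing justification for stopping the drug in the first place.

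Third, inclusion criterion 7 can be read as the patient's agreement to a restriction lasting the whole study. The patient information and any drug conversion plan are listed as attachments but are not in the documents, so what patients are told about stopping cannot be judged. No defect in the consent material can be claimed.

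Finally, the SD might prompt a reader to count how many placebo patients will have high untreated PTH. That concerns all placebo patients, whether or not they were treated before. It also depends on an assumed distribution and on trial patients resembling the local group. It does not measure this point.

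**Conclusion.** The point holds in a narrow form. Analogue users can enter, their drug is stopped at week 0, and by fair inference those on placebo stay off it for about 30 weeks, or about 17 in the additional arm. The statement on stopping ends with the washout. The 6-month statement rests on a local median and does not address withdrawal of existing SHPT treatment.

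The size is small. The protocol expects very few such patients, says that vitamin D is not routinely given in early CKD, and does not say why any entrant would be on an analogue. At assumed rates of 1% to 5%, this is 0.4 to 2 of 40 placebo patients. A reader might infer that patients are harmed or that the protocol forbids restarting treatment; the documents show neither. This is an inexpensive improvement worth considering, not a flaw that threatens the trial. The conclusion rests on two readings: that the safety statement in Prior and Concomitant Therapies refers to the 2-week washout, and that no restart is intended.

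**What to change.** Add one exclusion beside items 1 and 2 of Exclusion Criteria: currently prescribed alfacalcidol, calcitriol or another vitamin D analogue for secondary hyperparathyroidism. Keep the 2-week washout for other vitamin D products, including those bought over the counter. Appendix 1 carries the exclusions over, so the line should apply to the additional arm as well.

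The cost is one line, slightly narrower eligibility, and about 1, 2 or 5 more otherwise eligible patients to reach 80 at the assumed rates of 1%, 2% or 5%. No visit or test is added.

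A rule allowing open-label SHPT treatment during the trial is not recommended as part of this change. It could put an active analogue on top of blinded ergocalciferol while the weekly doses of the first month are taken at home, and it would sit awkwardly with inclusion criterion 7.

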## Local Regulations/Declaration of Helsinki

I will ensure that this study is conducted in accordance with the Principles of the “Declaration of Helsinki” (as amended in Tokyo (1975), Venice (1983), Hong Kong (1989), South Africa (1996)). <http://www.wma.net/e/policy/b3.htm> or with the laws of the country in which the research is conducted, whichever accords greater protection to the individual. The study must fully adhere to the principles outlined in the Guidelines for Good Clinical Practice” ICH Tripartite Guideline (January 1997)

## Informed Consent (any special conditions ie emergency situations?)

All subjects will provide written informed consent before enrolling in this trial. A full explanation of the study aims and procedures will be given in writing and explained face-to-face by the chief investigator. Patients will have at least 24 hours to decide on their participation. It will be made clear that patients can refuse to participate and withdraw from the trial at any stage for any reason. If any new information becomes available about any of the study drugs or techniques, patients will be informed and if this information changes the risk /benefit profile of the trial, a new consent form will be issued and informed consent will be obtained. Patients will be informed that the trial investigators may need to release clinical details of a patient to other health care professionals in an emergency situation relating to the trial. The date of informed consent will be documented in the CRF. The patients will be given a copy of the consent form.

## Independent Ethics Committee

All relevant information and forms will be submitted to an external ethics committee by the investigators.

This protocol and the accompanying material given to a potential patient (Patient Information Sheet, Consent form and GP letter) as well as any advertising material will be submitted by the Investigator to an Independent Ethics Committee in the UK. Full approval by the Committee will be obtained prior to starting the study and will be fully documented by letter to the Chief Investigator naming the study site, local PI (who may also be the Chief Investigator) and date the Committee deemed the study as permissible at that site.

# Study Finances

## Funding Source

All costs associated with this study will be covered wholly by:

Barts and the London Trust

Royal London Hospital

[name]

London

[name]

Contact: [name], Department head

## Indemnity for the performance of the study

This trial will be covered by standard NHS negligence idemnity

## Subject Payments

Subjects will not receive payment for this trial

# Sponsorship

Barts and the London NHS trust, [name]

# Publication Plan

The trial results will be published in a peer reviewed journal on completion of the study. Manuscripts for publication (abstract and full text articles) will be reviewed by the principal investigator and be made available to the Sponsor for review prior to submission.

**Attachments**

This section should contain all pertinent documents associated with the management of the study. The following is a list of attachments, those with an astrix* must be submitted to the Ethics Committee with the protocol.

[figure not shown]
 Consent Form*

[figure not shown]
 Information Sheet*

[figure not shown]
 GP letters / advertisement / any other letters/documents to be given/sent to subjects/patients*

[figure not shown]
 Layman’s Summary*

[figure not shown]
 Peer Review both Internal and External*

[figure not shown]
 Investigator Agreement (for any investigator, other than sponsor-investigator, who participates in the study)*

- Study Procedures Flowchart/Table
- Case Report Form
- Core Lab Instructions To Investigators
- Specimen Preparation And Handling (e.g. for any specialized procedures that study team must follow to process a study specimen, and/or prepare it for postage/courier/shipment)
- Drug Conversion Plan (e.g. if there is a special regimen for transitioning a subject from their baseline medication over to study medication)
- Antidote Preparation And Delivery (e.g. special instructions for preparing and delivering any therapy designed to reverse the effects of the study drug, if applicable)
- Study Plan Flowchart
- Source Data Identification List
- Study costing

Standard operating procedures

Pulse wave velocity

1. Subjects will be assessed using the VICORDER - PORTABLE CARDIO-VASCULAR TESTING SMART MEDICAL UK
2. In a quiet, temperature controlled room, patients will be placed at 45 degrees supine on an examination couch
3. PWV measures will be taken from carotid artery to brachial artery and femoral artery using both left and right sided sites
4. Each measure will be repeated twice
5. A tape measure will be used to measure the distance between each BP cuff
6. As per section 7, patients will be asked to refrain from caffeinated beverages or nicotine intake for four hours prior to assessment

Skin autofluorescence

1. Subjects will be assessed using the DiagnOptics’ AGE Reader (Netherlands)
2. This will be connected to a standard personal laptop computer
3. Patients will be assessed in the same environmental conditions (and just after) pulse wave velocity assessment
4. Forearm skin (left and right) will be gently cleaned with an alcohol based swab and any dead skin will be removed by gently placing adhesive medical tape over the affected skin areas.
5. 2 readings will be taken from the left and right forearm

Iontophoresis

1. This will occur immediately after skin autofluorescence under the same environmental conditions
2. Iontophoresis will be conducted and measured by a MIC 2 controller and DRT4 LDF monitor (Moor instruments, UK)
3. Iontophoresis will be assessed in response to 1% AcH and 1% SNip.
4. Forearm skin (left and right) will be gently cleaned with an alcohol based swab and any dead skin will be removed by gently placing adhesive medical tape over the affected skin areas.
5. The following doses will be administered:

| **Current (mA)** | **ACH** | **SNip** |
| --- | --- | --- |
| 0 | 60 sec | 60 sec |
| 10 | 30 sec | 30 sec |
| 0 | 60 sec | 60 sec |
| 20 | 30 sec | 30 sec |
| 0 | 60 sec | 60 sec |
| 35 | 30 sec | 30 sec |
| 0 | 60 sec | 60 sec |
| 50 | 30 sec | 30 sec |
| 0 | 60 sec | 60 sec |
| 75 | 30 sec | 30 sec |
| 0 | 60 sec | 60 sec |

Sub lingual side stream dark field microscopy

1. Several recordings of the sublingual microcirculation will be made each of 60 seconds
2. This will be conducted by a side stream dark field imager (Microvision, UK)
3. Sterile probes will be used for each patient
4. The probe is inserted under the tongue for 60 seconds on 2 occasions 1 minute apart
5. Video images will be recorded for analysis at a later date

Blood samples

1. If required by protocol, venesection will occur under sterile conditions from the dominant arm.

A single sample of 100 mls will be taken at visits 3,4,6,9. At other visits, 20 mls of blood will be taken.

3. Labelling: Tubes will be labelled with the following information

Pt initials

Pt trial number

Date

Time

Protocol number

**4. Residual Samples:** All residual samples will be destroyed following completion of planned assays.

Urine samples

1. As required by the protocol, a ~25 ml mid stream urine sample will be collected

2. Urine samples will be split into two sterile containers. One sample will be analysed at the Royal London Hospital for urine PCR and Na. Another sample will be stored for future analysis in a -80 degree Celsius fridge at the Royal London Hospital. This will be centrifuged so only the acellular component is retained.

**3. Residual Samples:** All residual samples will be destroyed following completion of planned assays.

Other clinical samples

1. Cardiac MRI: To be conducted at the London Chest Hospital

This examination is carried out by specialist doctors and nurses.

The scan lasts approximately 1 hour and will measure left ventricular ejection fraction and left ventricular mass

2. Carotid ultrasound: To be conducted at the Royal London Hospital using a specialist vascular probe and ultrasound machine. 2 readings of carotid intimal thickness will taken from the left and right carotid arteries at visit 3 and 9. Mean values will be recorded. A specialist vascular ultrasound and probe are available. The software has a specific protocol for measuring carotid intimal media thickness.

3. ECG: To be conducted at the Royal London Hospital. Patients will be placed at 45 degrees supine in the same environmental conditions mentioned previously. A standard 12 lead ECG will be recorded.

4. 24 hour BP: This will be conducted as an outpatient on a day to suit the patient. Formal reports will be reviewed and mean BP measures entered in the CRF.

